### Trial design

The present study is a multi-site, parallel group, randomized controlled trial (RCT) comparing the effectiveness of the E-E video against an APC video or no video (Fig. 1) [9]. Randomization is at a 1:1:1 ratio for the three arms of the trial. Nested within each arm of the trial is a list experiment. Participants will be randomized at a 1:1 ratio to a control or treatment list. After completing the list experiment, participants in arms 2 and 3 will receive the E-E video to ensure post-trial access to treatment [10].

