### Sample size

We calculated the sample size needed for pairwise comparisons between three groups using a one-way analysis of variance (ANOVA). The formula to calculate the sample size is [18]:

$$ {n}_A=\left({\sigma}_A^2+{\sigma}_B^2/\kappa \right){\left(\frac{Z_{1-\frac{\alpha }{\tau }}+{Z}_{1-\beta }}{\mu_A-{\mu}_B}\right)}^2 $$where *κ* = 1, which is the matching ratio; *μ*_*A*_ and *μ*_*B*_ are the group A and B means; *σ*_*A*_ and *σ*_*B*_ are the group A and B standard deviations; *α* = 0.05 is the type-I error; *β* = 0.20 is the type-II error; *Z* is the quantile function; and *τ* = 2 is the number of comparisons to be made. To detect a small difference of 0.1 between the knowledge scores of two trial arms, we assumed a mean of *μ*_*A*_ = 14.0 and *μ*_*B*_ = 14.1 and *σ*_*A*_ = 1.5 and *σ*_*B*_ = 1.5. We select *μ* on the expectation that participants will get 14 out of 18 knowledge items correct. This gives a sample size of *n*_*A*_ = *n*_*B*_ = *n*_*C*_ = 3,532, so *N* = 10,596. If we change our assumption about *σ* and increase it to *σ* = 1.8, then the required sample size becomes *n*_*A*_ = *n*_*B*_ = *n*_*C*_ = 5,087 and *N* = 15,261. For the list experiment, we selected a sample size to detect a small difference of 0.05 between the control list group and the treatment list group. Because we framed the list questions to avoid floor and ceiling effects, we expect, on average, that the control group will agree with 2 out of the 5 items and the treatment group 2.05 of the 6 items. We selected *σ*_*A*_ = 0.7 and *σ*_*B*_ = 0.8, allowing the second *σ* to be larger because of the additional sensitive item. This calculation gives a sample size of *n*_*A*_ = *n*_*B*_ = *n*_*C*_ = 3,548 and *N*= 10,644. If we change our assumption about *σ* and increase it to *σ*_*A*_ = 0.9 and *σ*_*B*_ = 1.0, then we have *n*_*A*_ = *n*_*B*_ = *n*_*C*_ = 4,553 and *N* = 13,659. For this study, we will recruit 17,010 participants, more than the 15,261 calculated sample size, to ensure our study is sufficiently powered.

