#### Primary outcomes

For each participant, we will sum the knowledge items that are correctly answered (min. = 0, max. = 18). We will then obtain the mean knowledge score for each trial arm. Let $$ {\overline{K}}_k $$ denote the mean knowledge score for the *k*th trial arm, where *k* ∈ {*v*, *a*, *c*} such that *v* represents the CoVideo, *a* represents the APC, and *c* represents the control. We will use an ordinary least squares (OLS) regression model to estimate $$ {\overline{K}}_k $$ as well as obtain the difference estimators. We define the difference between the CoVideo ($$ {\overline{K}}_v\Big) $$ and the control ($$ {\overline{K}}_c\Big) $$ as the total effect, the difference between the CoVideo ($$ {\overline{K}}_v\Big) $$ and the APC ($$ {\overline{K}}_a\Big) $$ as the content effect, and the difference between the APC video ($$ {\overline{K}}_a\Big) $$ and the control ($$ {\overline{K}}_c\Big) $$ as the attention effect.

For each list experiment, we will calculate the mean score for the control list, denoted by $$ \overline{C_i} $$, and the mean score for the treatment list, denoted by $$ \overline{T_i} $$, for the *i*th list experiment (*i* = 1, …, 5). We will then estimate the difference between the treatment and control list for each trial arm, denoted by $$ {D}_{ik}={\overline{T}}_{ik}-{\overline{C}}_{ik} $$, for the *i*th treatment list and *k*th trial arm, where *k* ∈ {*v*, *a*, *c*}. Let $$ D{D}_i^T $$ denote the total effect, which is estimated by *D*_*iv*_ − *D*_*ic*_; let $$ D{D}_i^C $$ denote the content effect, which is estimated by *D*_*iv*_ − *D*_*ia*_; and let $$ D{D}_i^A $$ denote the attention effect, which is estimated by *D*_*ia*_ − *D*_*ic*_. These analyses are analogous to difference-in-difference analyses, which can be implemented by specifying the appropriate main and interaction terms in an OLS regression.

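### The list-experiment sample size is worked out for the treatment-list minus control-list difference, not for the between-arm difference-in-differences that measures the video's effect on intent

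*Protocol article*

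**What the plan says.** The Sample size section (Protocol article) gives a two-group formula with a type-I error of 0.05 divided by τ = 2, 80% power and equal groups. For the list outcome it states that "we selected a sample size to detect a small difference of 0.05 between the control list group and the treatment list group", with expected means of 2 and 2.05 and SDs of 0.7 and 0.8. It reports 3,548 for each of three groups, 10,644 in all. A second scenario, with SDs printed as 0.9 and 1.0, is reported as 4,553 per group and 13,659 in all. The section closes: "we will recruit 17,010 participants, more than the 15,261 calculated sample size, to ensure our study is sufficiently powered". The 15,261 in that sentence is the larger of the two knowledge-score totals.

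Trial design sets three arms at 1:1:1 and, within each arm, "Participants will be randomized at a 1:1 ratio to a control or treatment list".

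Statistical methods, Primary outcomes, defines D as the treatment-list mean minus the control-list mean in an arm. It then defines the total, content and attention effects as differences in D between two arms, and adds: "These analyses are analogous to difference-in-difference analyses".

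**The concern.** The contrast that is sized and the contrast that answers the question are different quantities. By the worked example under Primary outcome measures, where means of 2 and 2.2 imply a prevalence of 20%, means of 2 and 2.05 imply that 5% endorse the sensitive item. Showing that this is not zero says nothing about the video. Objective 2 asks whether the video increases intent, and only DD addresses that.

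DD is also harder to estimate. It combines four cell means instead of two, and each cell holds one sixth of the sample. The factor of three does not fit either: the calculation compares two list groups, while the design has six arm-by-list cells.

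Intent is one of two primary outcomes, and the Discussion refers to the list experiment as the primary outcome of the study. The protocol states no decision rule for DD. Even so, a reader told that the study is sufficiently powered may take a null result on intent as stronger evidence against a small effect than the design can give.

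**Working it through.** **Inputs.** From Sample size: α/τ = 0.025, so Z = 1.960 (numerically the same as one two-sided 5% test); 80% power, Z = 0.8416; κ = 1; list difference 0.05; SDs 0.7/0.8 and, as printed, 0.9/1.0; N = 17,010. From Trial design: 1:1:1 to arms and 1:1 to lists within arm, so 17,010/6 = 2,835 per cell. Assumed here: SDs equal across arms, no covariate adjustment, no dropout, one list and one contrast.

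**1. The plan's own figures.** n = (σA² + σB²) × (1.960 + 0.8416)² / 0.05², where (2.8016)² = 7.849 and 7.849/0.0025 = 3,139.6.

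- SDs 0.7/0.8: 1.13 × 3,139.6 = 3,547.7, rounded up to 3,548; × 3 = 10,644. This reproduces exactly and shows that n is the size of one list group for a single list difference.
- SDs 0.9/1.0: 1.81 × 3,139.6 = 5,682.6, rounded up to 5,683; × 3 = 17,049. The protocol prints 4,553 and 13,659.
- SDs 0.8/0.9: 1.45 × 3,139.6 = 4,552.4, rounded up to 4,553; × 3 = 13,659. The printed result belongs to these SDs.

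The text does not settle which SDs were meant, so all three pairs are carried below.

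**2. The contrast that measures the video's effect.** Var(DD) = 2(σA² + σB²)/2,835. Power at 0.05 is Φ(0.05/SE − 1.960). The DD detectable with 80% power is 2.8016 × SE.

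| SDs | SE(DD) | Detectable DD, 80% power | Power if DD = 0.05 |
|---|---|---|---|
| 0.7/0.8 | √(2 × 1.13/2,835) = 0.0282 | 0.079 | 42.5% |
| 0.8/0.9 | √(2 × 1.45/2,835) = 0.0320 | 0.090 | 34.6% |
| 0.9/1.0 | √(2 × 1.81/2,835) = 0.0357 | 0.100 | 28.8% |

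The last column applies the plan's 0.05 to DD, which the plan itself does not do.

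**3. The contrast as literally worded.** The section does not say whether the two lists are compared within an arm or over all arms.

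- Within one arm (2,835 per list), power for a list difference of 0.05 is 70.7% at 0.7/0.8 and 50.8% at 0.9/1.0. Having 3,548 per list in every arm would take 6 × 3,548 = 21,288 participants.
- Pooled over arms (8,505 per list), it is 99.1% at 0.7/0.8 and 92.9% at 0.9/1.0. Pooling removes the comparison between arms, so this estimates no effect of the video.

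**The case against.** A reader might infer that the protocol promises 80% power for a 0.05 effect of the video on intent and delivers 43%. The documents do not support that. The 0.05 is attached only to the difference between the two lists, and no target for DD appears anywhere. The closing sentence compares 17,010 with the knowledge-score figure of 15,261 and does not claim 80% power for any list effect. On the pooled reading, the contrast actually sized is well powered. The base-case arithmetic is right, DD remains a valid estimator, and a DD of about 0.08 to 0.10 is detectable with 80% power.

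All of that stands, and it limits the point to a mismatch between the sizing and the estimand. It does not remove the mismatch. If 0.05 was not meant for DD, then the primary effect on intent has no sizing at all, while the text still assures the reader that the study is sufficiently powered. Nor is this a detail left to an analysis plan: the article prints a calculation for one quantity and defines its primary effect as another.

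**Conclusion.** Wrong as written. The list-experiment calculation and the statement of sufficient power do not apply to the difference-in-differences that answers objective 2.

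The firm result is the detectable DD with 80% power at 17,010 participants: about 0.079, 0.090 or 0.100, depending on the SDs. Power of about 43%, 35% or 29% holds only if 0.05 is adopted as the DD target.

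These figures rest on the assumptions listed with the inputs and on no correction for multiplicity. Correcting for three contrasts would lower power at 0.05 to 26.7% (0.7/0.8) or 16.0% (0.9/1.0). The 0.7/0.8 figures follow from inputs that reproduce exactly. The larger-SD figures depend on resolving the conflict over 4,553.

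**What to change.** 1. First reconcile the second list scenario. Either the SDs are 0.8/0.9 and 4,553 stands, or they are 0.9/1.0 and the figure is 5,683 per group. Under the plan's own factor of three the latter becomes 17,049, which is above both 15,261 and the planned 17,010.
2. Keep N = 17,010. Replace the list-experiment calculation with one for DD, using six cells of 2,835 and Var(DD) = 2(σA² + σB²)/2,835.
3. State the DD detectable with 80% power for each SD scenario retained, and the power at 0.05 with 0.05 labelled as an assumed DD target.
4. Do not present 10,644, 13,659 or 17,010 as giving 80% power for a 0.05 effect of the video on intent.

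The cost is a text change and a less favourable stated detectable effect. No participants are added and the analysis is unchanged. Trial status reports 14,800 completed surveys, so the design itself is close to settled.

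### The larger-SD list scenario does not fit its own formula: SDs 0.9 and 1.0 give 5,683 per group (N = 17,049), while the printed 4,553 (N = 13,659) belongs to SDs 0.8 and 0.9

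*Protocol article*

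**What the plan says.** The Protocol article, Sample size, gives one formula for all its calculations: the sum of the two variances (the second divided by κ), times the squared ratio of the two normal quantiles' sum to the mean difference. The inputs are stated beside it: κ is "1, which is the matching ratio", α = "0.05 is the type-I error", β = "0.20 is the type-II error", and τ, which divides α, = "2 is the number of comparisons to be made".

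Four results follow. Two are for the knowledge score (difference 0.1): 3,532 per group with SD 1.5 and 5,087 with SD 1.8, so N = 10,596 and 15,261. Two are for the list experiment, which is sized "to detect a small difference of 0.05 between the control list group and the treatment list group", on the expectation that "the control group will agree with 2 out of the 5 items and the treatment group 2.05 of the 6 items". With SDs 0.7 and 0.8 the result is 3,548 per group, N = 10,644. With SDs raised to 0.9 and 1.0 it is "4,553 and *N* = 13,659".

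The section closes: "we will recruit 17,010 participants, more than the 15,261 calculated sample size, to ensure our study is sufficiently powered".

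**The concern.** The step from SDs 0.7/0.8 to 0.9/1.0 raises the sum of variances from 0.49 + 0.64 = 1.13 to 0.81 + 1.00 = 1.81, a factor of 1.60. With everything else fixed, n should rise by the same factor, from 3,548 to roughly 5,680. The printed figure rises by a factor of only 4,553/3,548 = 1.28. So the SDs and the sample size given for this scenario cannot both be right.

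The list experiments measure behavioral intent, one of the trial's two primary outcomes, and the recruitment target is defended by comparison with the calculated sizes. The figure used for that comparison, 15,261, is the largest of the four as printed. If the larger-SD list scenario really needs more than that, the comparison rests on the wrong number.

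**Working it through.** **Inputs** (all from the Protocol article, Sample size): α = 0.05, τ = 2, β = 0.20, κ = 1; difference 0.1 for knowledge and 0.05 for the lists; SDs as listed below.

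**Formula**, as the section gives it, with κ = 1:

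n = (σ_A² + σ_B²) × [(z(1 − α/τ) + z(1 − β)) / (μ_A − μ_B)]², rounded up, and N = 3n.

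The quantiles are z(0.975) = 1.95996 and z(0.80) = 0.84162. Their sum squared is 7.849.

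**Step 1: the three figures that reproduce.**

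- Knowledge, SDs 1.5/1.5: (2.25 + 2.25) × 7.849/0.01 = 3,532.0, so 3,532 and N = 10,596. Agrees.
- Knowledge, SDs 1.8/1.8: (3.24 + 3.24) × 7.849/0.01 = 5,086.1, so 5,087 and N = 15,261. Agrees.
- List, SDs 0.7/0.8: (0.49 + 0.64) × 7.849/0.0025 = 3,547.7, so 3,548 and N = 10,644. Agrees.

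The formula, the inputs and the rounding rule are therefore being read as the plan used them.

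**Step 2: the figure that does not.**

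- List, SDs 0.9/1.0: (0.81 + 1.00) × 7.849/0.0025 = 5,682.6, so 5,683 and N = 3 × 5,683 = 17,049. The plan prints 4,553 and 13,659.
- Gap: 5,683 − 4,553 = 1,130 per group (1,130/5,683 = 19.9%), and 17,049 − 13,659 = 3,390 in total.

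**Step 3: where 4,553 comes from.**

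- List, SDs 0.8/0.9: (0.64 + 0.81) × 7.849/0.0025 = 4,552.4, so 4,553 and N = 13,659. Exact match.
- Keeping SDs 0.9/1.0 and changing the error rates does not give 4,553. With τ = 1 and 80% power the result is 4,476; with τ = 2 and 70% power it is 4,469. Both also contradict the stated τ or β, under which the other three figures reproduce.

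**Step 4: what it means for the target.** Recruiting 17,010 gives 17,010/3 = 5,670 per arm.

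- If SDs 0.8/0.9 were meant: the largest of the four sizes is 15,261, and 17,010 − 15,261 = 1,749 to spare.
- If SDs 0.9/1.0 were meant: the largest is 17,049, and 17,010 − 17,049 = −39. With 5,670 per group the standard error is √(1.81/5,670) = 0.01787, and power is Φ(0.05/0.01787 − 1.96) = Φ(0.838), about 79.9%.
- For comparison, 4,553 per group with SDs 0.9/1.0 would give about 70.8% power. The trial is not recruiting to that number.

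**The case against.** The strongest reply is that the SDs, not the sample size, may be the misprint. The pair 0.8/0.9 is one step of 0.1 above the base pair 0.7/0.8, it yields 4,553 exactly, and the printed n and N agree with each other (3 × 4,553 = 13,659). On that reading the calculation is sound, 15,261 is the largest requirement, and the closing sentence is correct. This objection stands: nothing in the article decides between the two readings.

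A second reply is that little depends on it. The scenario is a sensitivity case; the base list case needs only 10,644. Even if 0.9/1.0 was meant, the shortfall is 39 of 17,049 (0.2%) and power drops by about 0.1 percentage point. The 20% understatement describes the printed figure, not the trial's power, because recruitment was set at 17,010 and not at 13,659. This also stands, and it limits the consequence. It does not remove the inconsistency, which remains on either reading.

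It can also be said that the closing sentence never calls 15,261 the largest requirement. That is true. It is, however, the largest of the four printed figures, and the comparison supports the power claim only if no scenario needs more.

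**Conclusion.** The larger-SD list scenario is internally inconsistent. Under the plan's own formula and inputs, SDs 0.9/1.0 require 5,683 per group and N = 17,049; the printed 4,553 and 13,659 are the result for 0.8/0.9. This rests on no assumption beyond the section's own inputs, and the other three figures confirm that reading.

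A reader might infer that the target of 17,010 falls below the plan's requirement and that the claimed margin of 1,749 does not exist. The document supports this only if 0.9/1.0 was meant, and then the deficit is 39 participants, with power of about 79.9% on the plan's three-group counting.

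A reader might also multiply 5,683 by the six list groups (three arms, two lists each, per Trial design) and conclude that 34,098 are needed. That raises a separate question, whether n applies per arm or per list group within an arm. The mismatch between these SDs and this n neither depends on it nor settles it, so 34,098 is no measure of this error.

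**What to change.** In the Protocol article, Sample size, state which SDs the larger-SD list scenario used and print the matching n and N.

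- If 0.8 and 0.9 were used: correct the two SDs. The figures 4,553 and 13,659, and the closing comparison of 17,010 with 15,261, then stand unchanged.
- If 0.9 and 1.0 were used: correct the figures to 5,683 and 17,049. Reword the closing sentence to say that 17,010 exceeds three of the four calculated sizes and falls 39 short of the fourth, giving about 79.9% power in that scenario on the plan's three-group counting.

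The cost is a line or two of text. No additional participants and no change to the analysis are needed on either reading.

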### Recruitment

To be recruited, a person must open an account on ProA and provide his or her personal information. Participants must agree to ProA’s data privacy terms and conditions. ProA will assign each participant a unique, anonymized ID. The study investigators will also open an account on ProA. We will instruct the ProA platform on how many participants need to be recruited. ProA will filter out all participants who do not meet the eligibility criteria. Participant recruitment will happen on a “first come, first served” basis until the recruitment number (sample size) is reached. We will compensate the participants an equivalent of £1 for the expected 10-min completion time.

### Assignment of interventions: allocation

The Gorilla platform is designed to host and implement online experimental studies (implementation). Gorilla will randomly allocate participants to the intervention (CoVideo), placebo (APC), or control (no video) arm (sequence generation). Gorilla will use a web-based randomization algorithm, which is unknown to us (concealment mechanism).

### Assignment of interventions: blinding

#### Who will be blinded

The study investigators and those involved in the data analyses and statistics will be blinded to the group allocation.

### Data collection and management

#### Plans for assessment and collection of outcomes

Data will be collected on the Gorilla platform. Participants will submit data by clicking on the response buttons. We expect to collect the data over a 4-week period.

#### Plans to promote participant retention and complete follow-up

Participants will automatically exit the study if they take longer than 45 min to complete the survey. The time-out is to ensure that participants do not clog up the system with incomplete surveys. Since the participants are anonymous to us, there is no way to initiate follow-up in the time limit.

#### Data management

Gorilla will store the trial data on its cloud platform, hosted on Microsoft Azure in the Republic of Ireland. The Gorilla database is encrypted using industry-standard cryptography. The study investigators own the research data that has been collected using Gorilla and have complete control over it. The study investigators can generate and access the completely anonymized data from the Gorilla platform. The data will be downloaded and safely stored for statistical analysis on a computing system maintained by the University of Heidelberg in Germany.

#### Confidentiality

The participants, who are completely anonymous to us, will have no identifying information associated with their unique IDs. We will inform participants that if they email the study investigators then their names could be revealed to us. The study investigators will keep this information confidential.

### Statistical methods

#### Descriptive measures

We will use descriptive statistics to obtain the mean and standard deviation of age, the proportion of participants by gender, and frequency distributions for country of residence and education status.

#### Primary outcomes

For each participant, we will sum the knowledge items that are correctly answered (min. = 0, max. = 18). We will then obtain the mean knowledge score for each trial arm. Let $$ {\overline{K}}_k $$ denote the mean knowledge score for the *k*th trial arm, where *k* ∈ {*v*, *a*, *c*} such that *v* represents the CoVideo, *a* represents the APC, and *c* represents the control. We will use an ordinary least squares (OLS) regression model to estimate $$ {\overline{K}}_k $$ as well as obtain the difference estimators. We define the difference between the CoVideo ($$ {\overline{K}}_v\Big) $$ and the control ($$ {\overline{K}}_c\Big) $$ as the total effect, the difference between the CoVideo ($$ {\overline{K}}_v\Big) $$ and the APC ($$ {\overline{K}}_a\Big) $$ as the content effect, and the difference between the APC video ($$ {\overline{K}}_a\Big) $$ and the control ($$ {\overline{K}}_c\Big) $$ as the attention effect.

For each list experiment, we will calculate the mean score for the control list, denoted by $$ \overline{C_i} $$, and the mean score for the treatment list, denoted by $$ \overline{T_i} $$, for the *i*th list experiment (*i* = 1, …, 5). We will then estimate the difference between the treatment and control list for each trial arm, denoted by $$ {D}_{ik}={\overline{T}}_{ik}-{\overline{C}}_{ik} $$, for the *i*th treatment list and *k*th trial arm, where *k* ∈ {*v*, *a*, *c*}. Let $$ D{D}_i^T $$ denote the total effect, which is estimated by *D*_*iv*_ − *D*_*ic*_; let $$ D{D}_i^C $$ denote the content effect, which is estimated by *D*_*iv*_ − *D*_*ia*_; and let $$ D{D}_i^A $$ denote the attention effect, which is estimated by *D*_*ia*_ − *D*_*ic*_. These analyses are analogous to difference-in-difference analyses, which can be implemented by specifying the appropriate main and interaction terms in an OLS regression.

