#### Secondary outcomes

Using the same statistical procedure described above, we will assess behavioral intent to seek health information with E-E media. To establish participant engagement with the CoVideo, we will use a logistic regression model to estimate the proportion of participants in the APC and control arms that chose to watch the CoVideo, adjusting for the knowledge scores and demographic factors. We will use either an OLS model or Cox proportional hazards model to model the time to when a person clicks “Finish Video” (right censoring) or when the CoVideo ends naturally (left censoring). We will use R statistical software to undertake the analysis.

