#### Methods for additional analyses (e.g., subgroup analyses)

We will conduct both country-specific and cross-country pooled analyses, provided sufficient sample sizes can be recruited from each country.

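### The primary OLS models are specified without covariates; pre-specifying country, age, gender and education would give a modest gain in precision at little cost

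*Protocol article*

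**What the plan says.** The Primary outcomes section under Statistical methods gives both primary estimators explicitly.

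- **Knowledge:** "We will use an ordinary least squares (OLS) regression model to estimate" the mean score in each arm. The total, content and attention effects are the pairwise differences of those means.
- **Lists:** within each arm, the control-list mean is subtracted from the treatment-list mean to give D. The effects are the differences of D between arms (DD), "which can be implemented by specifying the appropriate main and interaction terms in an OLS regression".

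Neither description names a covariate, and neither says that covariates are excluded.

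Elsewhere in Statistical methods:

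- Descriptive measures lists "the mean and standard deviation of age, the proportion of participants by gender, and frequency distributions for country of residence and education status".
- Secondary outcomes fits the logistic model for choosing to watch the video "adjusting for the knowledge scores and demographic factors".
- Methods for additional analyses says "We will conduct both country-specific and cross-country pooled analyses", provided enough participants are recruited in each country.

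**The concern.** Knowledge scores and list counts may well differ by country, age, gender and education. In a pooled analysis of six countries, a model with arm and list terms alone leaves that variation in the residual, and every standard error carries it. Adjusting a randomised comparison for characteristics that a video of about two and a half minutes cannot change removes part of this variation without biasing the effect.

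The between-arm list effect is where precision is scarcest, because it combines four cell means. A second stake is analytic freedom. If the covariates are not fixed in advance, an adjusted and an unadjusted result could both later be presented as primary.

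**Working it through.** **Inputs from the Sample size and Trial design sections.** The article states that "0.05 is the type-I error" and that "0.20 is the type-II error". With τ = 2 the critical value is z at 0.975, so the multiplier is 1.960 + 0.842 = 2.802. Total N is 17,010, allocated 1:1:1 to arms and 1:1 to lists within arm. An even split gives 17,010/3 = 5,670 per arm and 5,670/2 = 2,835 per arm-by-list cell. Knowledge: difference 0.1, SD 1.5 or 1.8. Lists: SDs 0.7 and 0.8, or 0.9 and 1.0.

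**Input not in the document.** R² is the share of outcome variance that country, age, gender and education explain. I assume 0.05 to 0.10, the same in every cell, and also show 0.20.

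**Step 1: the plan's own figures.** The formula is n = (σ_A² + σ_B²) × (2.802/difference)².

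- Knowledge, SD 1.5: 3,532 (stated 3,532).
- Knowledge, SD 1.8: 5,087 (stated 5,087).
- List, SDs 0.7 and 0.8: (0.49 + 0.64) × (2.802/0.05)² = 3,548 (stated 3,548).

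These three reproduce. The fourth, 4,553 for SDs 0.9 and 1.0, does not: the formula gives 5,683, and 4,553 is what SDs 0.8 and 0.9 give. That is a separate matter and is not used below.

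**Step 2: list DD without covariates, SDs 0.7 and 0.8.**

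- SE(D) = √(1.13/2,835) = 0.0200.
- SE(DD) = √2 × SE(D) = 0.0282.
- DD detectable with 80% power = 2.802 × 0.0282 = 0.079.

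With SDs 0.9 and 1.0 the detectable DD is 0.100.

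**Step 3: with covariates.** The residual variance is multiplied by (1 − R²) and the standard error by √(1 − R²).

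| Assumed R² | Detectable DD, SDs 0.7/0.8 | Detectable DD, SDs 0.9/1.0 | Knowledge power, SD 1.5 | Knowledge power, SD 1.8 |
|---|---|---|---|---|
| 0 | 0.079 | 0.100 | 94.4% | 84.1% |
| 0.05 | 0.077 | 0.098 | 95.4% | 85.9% |
| 0.10 | 0.075 | 0.095 | 96.3% | 87.7% |
| 0.20 | 0.071 | 0.090 | 97.8% | 91.1% |

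The equivalent number of extra participants is 17,010/(1 − R²) − 17,010, which is 895 at R² = 0.05 and 1,890 at R² = 0.10.

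**Step 4: does this rescue the list comparison?** The article states no target for DD. Its 0.05 is the difference between treatment list and control list. If 0.05 is borrowed as a DD purely for illustration:

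- SDs 0.7 and 0.8: power is 42.5% unadjusted, 44.3% at R² = 0.05 and 46.3% at R² = 0.10.
- SDs 0.9 and 1.0: power is 28.7%, 30.0% and 31.4%.
- Reaching 80% would need R² of about 0.60 or 0.75, or about 42,600 or 68,200 participants.

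**The case against.** The strongest reply is that nothing stated is wrong. Differences of means under this randomisation are unbiased, and choosing an adjusted primary analysis is a preference for efficiency. This stands.

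The next reply is that a covariate list usually belongs in an analysis plan that is not shown here. A reader might infer that the primary models deliberately contain nothing but arm and list terms. The text does not go that far: it specifies only those terms and is silent on others. Two things weaken the reply without removing it. The article describes itself as the full protocol, and it states adjustment where it intends it, in the secondary logistic model. That contrast is not a contradiction, since the logistic model describes who chooses to watch the video and is not a comparison of the CoVideo with its controls.

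A reader might also infer that adjustment would repair the power of the list outcome. Step 4 shows that it would not. The shortfall arises because the list sample size is set on the difference between two lists while the effect of interest compares that difference between arms. That should be judged as a sizing question.

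Two further replies stand in part. Knowledge already has 84% to 94% power for its stated difference. Country is not ignored, because country-specific analyses are planned. Neither reply gives a reason to leave country out of the pooled model.

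Finally, adjustment is not entirely free: covariate coding and the handling of missing values must be fixed in advance.

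**Conclusion.** The point holds as a minor recommendation. The primary effects are specified as unadjusted differences of means although suitable covariates are available. Pre-specified adjustment would be somewhat more precise and equally free of bias from the randomisation.

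At an assumed R² of 0.05 to 0.10, residual variance falls by 5% to 10%, and the detectable list DD falls by about 0.002 to 0.004 (SDs 0.7 and 0.8). Knowledge power at SD 1.8 rises by about 2 to 4 percentage points. These figures rest on an R² that the document does not supply, on an even split of 17,010 participants, and on the covariates explaining a similar share of variance in each cell. If R² is near zero, the gain is near zero and nothing is lost. The document does not support calling the unadjusted analysis invalid or biased.

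**What to change.** Before the analysis, fix the following for the pooled primary models:

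1. Add country fixed effects and main effects for age, gender and education to the knowledge model and to each list model, keeping the arm, list and arm-by-list terms that define the effects.
2. Use heteroskedasticity-robust standard errors. The plan itself expects a larger SD on the treatment list.
3. State how each covariate is coded, and give a simple rule for missing values, such as a missing-indicator category, so that no randomised participant is dropped.
4. Do not carry the knowledge score over from the secondary model as a covariate for the list effects, because it is itself an outcome of the randomised arms.
5. Report the unadjusted differences as a sensitivity analysis.

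The cost is some wording in the analysis plan and a few lines of R. No new data are needed beyond the variables already planned for description, and the degrees of freedom used are negligible at this sample size. The Trial status section reports 14,800 completed surveys, so the model can still be settled at a stage when recruiting many more participants would be hard.
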